### 3.3 Baseline Assessments

Patients' oral conditions will be assessed through the Decayed, Missing, and Filled Teeth Index (DMFT), Visible Plaque Index (VPI), and Gingival Bleeding Index (GBI). Next, with a millimeter probe, root exposure height will be measured as the distance between the apical limit of the cemento-enamel junction and the highest point of the free gingival margin. At this stage, the values will not be classified; scores will be established only after the complete sample has been obtained.

Root exposure height and sensitivity scores by VAS will be stratification variables in the randomization process. The tooth will be considered the sampling unit. Eligible teeth will be entered into an Excel spreadsheet according to root exposure height and mean sensitivity score. To ensure a homogeneous distribution of these two factors across study groups, teeth will be ordered by sensitivity scores and divided into two clusters: one with lower scores and the other with higher scores. These clusters will then be subdivided by smaller/larger exposure size, resulting in four groups: (a) lower sensitivity and smaller exposures, (b) lower sensitivity and larger exposures, (c) higher sensitivity and smaller exposures, and (d) higher sensitivity and larger exposures. This stratified randomization method was based on another parallel clinical trial. Stratification will be performed approximately every 48 selected teeth for methodological feasibility.

In cases where experimental treatments do not reduce dentin hypersensitivity, patients will receive the product with the best performance to avoid further damage.

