### 3.6 Statistical Analyses

The results of DMFT, VPI, GBI indices, and root exposure height will be presented descriptively. Correlation between the sensitivity assessment methods used (CoVAS and VAS) will be analyzed using Spearman's correlation coefficient. Comparisons among treatments at the same evaluation time and among time points within the same treatment will be analyzed using equality tests for two proportions, with a significance level of 5%.

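### Randomisation is stratified on baseline VAS and root exposure height, but the named between-treatment test adjusts for neither and is therefore conservative

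*Protocol*

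**What the plan says.** Section 3.3 of the protocol makes the two baseline measurements part of the design: "Root exposure height and sensitivity scores by VAS will be stratification variables in the randomization process". It gives the purpose and the first step: "To ensure a homogeneous distribution of these two factors across study groups, teeth will be ordered by sensitivity scores and divided into two clusters". The second step follows: "These clusters will then be subdivided by smaller/larger exposure size, resulting in four groups". On timing it says: "Stratification will be performed approximately every 48 selected teeth for methodological feasibility". With 192 teeth planned, that is about four batches.

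Section 3.6 names the test. Comparisons between treatments at one time, and between times within one treatment, "will be analyzed using equality tests for two proportions, with a significance level of 5" percent. The oral indices "and root exposure height will be presented descriptively". No stratum, covariate or batch term is mentioned. Baseline VAS enters only as one of the times compared within a treatment.

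Section 3.3 also says of the height measurements: "At this stage, the values will not be classified; scores will be established only after the complete sample has been obtained". It gives no cut-point for either factor, and does not say whether the splits are made within each batch or on the whole sample.

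**The concern.** Stratified allocation makes the arms more alike on the stratification factors than simple randomisation would. If those factors predict the outcome, the treatment difference truly varies less from one allocation to another. A test that ignores the factors still estimates its standard error from the full spread of the outcome, so it overstates the uncertainty. The real type I error falls below the nominal 5%, intervals are wider than they need to be, and power is lost. The trial would have the design work of stratification and the balance it brings, but not the precision that adjustment could add.

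This is more than a detail a protocol leaves to an analysis plan. Section 3.6 fixes a particular test, and a plain two-proportion test has no place for a covariate.

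**Working it through.** **1. The plan's own figure.** Section 3.2 gives a mean VAS difference of 0.210 at six months, alpha 0.05, power 0.80 and 48 teeth per group, but no SD. The 48 therefore cannot be reproduced, only solved backwards. Taking the test as two-sided and adding nothing for dropout:

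SD = 0.210 / [(1.960 + 0.842) × √(2/48)] = 0.210 / (2.802 × 0.2041) = 0.367

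The standardised difference is d = 0.210 / 0.367 = 0.572. This SD is an assumption chosen to give 80% power; it is not a protocol figure.

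**2. Gain from adjusting for measured baseline VAS.** Adjustment multiplies the residual variance by 1 − r². Power = Φ(d × √(48/2) / √(1 − r²) − 1.960), where d × √24 = 2.802. The equivalent unadjusted sample is 48 / (1 − r²). The correlation r is assumed.

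| r | 1 − r² | Equivalent teeth per arm | Power |
|---|---|---|---|
| 0 | 1.00 | 48.0 | 80.0% |
| 0.1 | 0.99 | 48.5 | 80.4% |
| 0.3 | 0.91 | 52.7 | 83.6% |
| 0.5 | 0.75 | 64.0 | 89.9% |
| 0.7 | 0.51 | 94.1 | 97.5% |

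Adjusting only for a two-level VAS stratum cut at the median has a variance factor of about 1 − (2/π)r². It gives 82.3%, 86.3% and 92.2% at r = 0.3, 0.5 and 0.7. Measured values recover more than labels do.

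**3. Simulation of the section 3.3 scheme.** The set-up was four batches of 48, halved by VAS rank and then by height rank, so that each batch has 48 / (4 strata × 4 arms) = 3 teeth per arm per stratum. One pair of arms was compared. Scores were normal, teeth independent, and height unrelated to outcome. There were 4000 runs per setting, so the Monte Carlo standard error of a 5% rate is √(0.05 × 0.95 / 4000) = 0.34 percentage points.

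| | r = 0.3 | r = 0.5 | r = 0.7 |
|---|---|---|---|
| Type I error, unadjusted t-test | 4.0% | 3.2% | 1.9% |
| Type I error, adjusted for VAS and height | 4.4% | 5.0% | 5.4% |
| Type I error, two-proportion test at an assumed median cut | 4.6% | 4.4% | 2.6% |
| Power, unadjusted t-test | 80% | 81% | 84% |
| Power, adjusted | 83% | 89% | 98% |
| Power, two-proportion test at that cut | 59% | 59% | 60% |

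The two-proportion test is conservative too, clearly so at r = 0.7 and within or near simulation error at the lower values. Its low power comes mainly from reducing the score to a proportion, not from omitting the strata.

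**4. Are the stratum labels usable as covariates?** If the cuts are made within each batch, about 12% of teeth would fall in a different one of the four strata than under whole-sample cuts, and about 5% would change their VAS label. This is a further reason to adjust for the measured values.

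**5. The height sentence.** One sentence of section 3.3 leaves height unclassified until all teeth are in; the next paragraph splits teeth into smaller and larger exposures about every 48. The two fit together only if the later scores are something other than the randomisation split. The text does not say so, but it cites one reference for the scoring and a different one for the stratified randomisation, which suggests two procedures.

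**The case against.** The strongest objection is that the power gains belong to an analysis the protocol does not plan. They compare a t-test with covariance analysis on continuous VAS, whereas section 3.6 plans a test of proportions. This stands. The gains follow only if the score is analysed as measured, and part of the benefit of the change comes from no longer dichotomising.

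The 80% starting point is also back-solved. With an assumed SD of 1 VAS point, power at 48 per arm is about 18% unadjusted and 22% adjusted at r = 0.5; with an SD of 2 it is about 8% and 9%. That stands as well: the direction is firm, but the size is conditional.

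Third, the error is conservative and covariate lists often sit in an analysis plan. The first half is right and limits the seriousness. The second half does not answer the point, because the test named in section 3.6 cannot take covariates.

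A reader might infer more than the protocol supports:
- That the stratification is wasted. It is not: balance on both factors is still delivered, and only the variance reduction in the test is lost.
- That baseline VAS is not used at all. It is a comparison time within each treatment; what is missing is adjustment between treatments.
- That section 3.3 contradicts itself beyond repair. A later descriptive score and a rank split within each batch can coexist, so this is an ambiguity.
- That this ambiguity costs precision. It does not; it leaves the strata unclear, which is a separate matter.

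**Conclusion.** The point holds as a recommended improvement. The between-treatment test in section 3.6 adjusts for neither stratification factor, so its standard errors are too large and it is conservative; validity is not threatened. Under the assumptions above, adjustment is worth almost nothing at r = 0.1 and the equivalent of 64 rather than 48 teeth per arm at r = 0.5, where power rises from 80% to about 90%. These figures assume a two-sided 5% test, the back-solved SD of 0.367, continuous VAS, no loss to follow-up and independent teeth. The last is doubtful: section 3.3 takes the tooth as the sampling unit and the eligibility criteria allow more than one tooth per patient. Any prognostic value of height itself would add to the gain and is not counted.

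**What to change.** In section 3.6, replace the two-proportion tests for between-treatment comparisons with a model of the measured score, one for VAS and one for CoVAS. Include as covariates the baseline value of the same scale, root exposure height in mm and randomisation batch, and allow for several teeth in the same patient, for example with a patient random effect. Use the measured values, not the four stratum labels.

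Separately, in section 3.3, say that the sentence "scores will be established only after the complete sample has been obtained" concerns only the later descriptive scoring of height, and that the lower/higher and smaller/larger splits for randomisation are made by rank within each batch of about 48 teeth. Splitting by rank keeps 3 teeth per arm per stratum. Fixing the cuts at the medians of the first batch would not do better: in simulation about 4.9% of teeth change VAS label against the overall median under either rule, and later batches would no longer divide evenly.

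The cost is a change of the named test and slightly more analysis work. All the variables are already collected.

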## **3. Materials and Methods**

### **3.1 Experimental Design**

This will be a parallel, prospective, randomized clinical trial. Only the volunteers will remain blinded to the allocation group (single-blind design).

A sample of 192 teeth with exposed hypersensitive root dentin will be planned, with 48 teeth per group. The study factors will be: (1) desensitizing treatment at four levels

(Table 1): fluoride varnish (positive control, Duraphat – VF); solution containing crystalline bioactive ceramic (Biosilicate® – SS); self-etch adhesive system (Single Bond Universal – SB); and light-cured fluoride varnish (VL); and (2) evaluation times: baseline (prior to treatments), and 7, 15, and 30 days, as well as 6 and 12 months post-treatment. The response variables will be hypersensitivity assessment through the Visual Analog Scale (VAS) and the Computerized Visual Analog Scale (CoVAS).

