### 3.2 Sample Size Calculation and Patient Selection

Sample size was calculated based on a published study using Sigma Plot 12.0 software, with an expected mean difference in cervical dentin hypersensitivity levels (measured by VAS) of 0.210 after six months. Test details: significance level ( $\alpha$ ) = 0.05; test power ( $1-\beta$ ) = 0.80; dropout ( $\beta$ ) = 0.2. The final sample size was determined as 48 teeth per group.

Patients will be recruited from the undergraduate clinic of FOA-UNESP, aged between 20 and 70 years, with at least one root exposure, totaling 192 teeth with DH in non-cavitated root exposures (not requiring restoration), regardless of location in the dental arch. Teeth will be divided into three groups ( $n = 48$  teeth each) with a 5% significance level. Eligibility criteria are described in Table 2.

**Table 1.** Products to be used in the study and their composition according to the manufacturers

| Material                                                                                                                                                                                                                                                                          | Manufacturer                                  | Composition*                                                                                                                                                                           | Application*                                                                                                                                                                             |
|------------------------------------------------------------------------------------------------------------------------------------------------------------------------------------------------------------------------------------------------------------------------------------------|------------------------------------------------------|-----------------------------------------------------------------------------------------------------------------------------------------------------------------------------------------------|-------------------------------------------------------------------------------------------------------------------------------------------------------------------------------------------------|

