| Inclusion Criteria                                                                                                                                                                                   | Exclusion Criteria                                                                 |
|-------------------------------------------------------------------------------------------------------------------------------------------------------------------------------------------------------------|-------------------------------------------------------------------------------------------|
| -Age between 20–70 years, regardless of sex                                                                                                                                                                 | -Pregnant, lactating, or smoking patients                                                 |
| -Good general health; no history of allergies to dental products                                                                                                                                            | -Presence of active caries lesions                                                        |
| -Presence of at least one non-cavitated root exposure ( $\geq 1$ mm depth, not requiring restoration) presenting dentin hypersensitivity of at least grade 3 (VAS) to air-jet stimulation at 10 cm distance | -Use of desensitizing agents in the last 6 months                                         |
| -Absence of active periodontal disease                                                                                                                                                                      | -Active periodontal disease without treatment                                             |
|                                                                                                                                                                                                             | -Use of orthodontic appliances or removable prostheses with clasps on the evaluated tooth |
|                                                                                                                                                                                                             | -Parafunctional habits and occlusal trauma                                                |

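### One patient may supply several teeth, but the planned two-proportion tests ignore the patient and the repeated measurement of the same tooth; the direction of the error depends on an allocation rule the protocol does not state

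*Protocol*

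**What the plan says.** - **Unit.** Section 3.3: "The tooth will be considered the sampling unit". Teeth are listed, ordered by sensitivity and split by exposure height into four strata. The patient plays no part in this.
- **Teeth per patient.** Section 3.2 recruits patients "with at least one root exposure, totaling 192 teeth with DH in non-cavitated root exposures", and Table 2 asks for "Presence of at least one non-cavitated root exposure". That is a minimum. No maximum and no number of patients is given.
- **Size.** Section 3.1: "A sample of 192 teeth with exposed hypersensitive root dentin will be planned, with 48 teeth per group", with "desensitizing treatment at four levels". The calculation in section 3.2 has no term for clustering.
- **Outcome.** The patient marks the VAS and sets the CoVAS potentiometer (section 3.2).
- **Analysis.** Apart from descriptive summaries and Spearman's coefficient for VAS against CoVAS, section 3.6 names only "equality tests for two proportions, with a significance level of 5" per cent. These serve both the comparisons between treatments at one time and those between times within one treatment.
- **Allocation of several teeth from one patient.** Not stated. Section 3.3 describes sorting of teeth. Section 3.1 says "Only the volunteers will remain blinded to the allocation group", in the singular, which does not settle the matter.

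**The concern.** Two teeth in one mouth share a rater, a pain threshold, a diet and brushing habits, so their scores are likely to be correlated. A two-proportion test assumes independent observations. If several teeth come from one patient, its standard error matches the data only under some allocation schemes, and the protocol does not say which scheme applies. A reader therefore cannot tell whether the between-arm tests are liberal, conservative or merely inefficient.

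The comparison between time points has a second problem. It sets the same 48 teeth against themselves with a test meant for two separate samples.

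This is not a detail left open for a later plan. The protocol fixes the unit, the test and the sample size, and a SAP that modelled the patient would depart from section 3.6.

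**Working it through.** **Inputs from the protocol:** 192 teeth, 4 arms of 48, alpha 0.05, power 0.80, six assessments of each tooth. **Assumptions, because the protocol gives neither:** m = 2 to 4 teeth per patient and intra-patient correlation (ICC) r = 0.3 to 0.5.

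**The stated 48.** It cannot be reproduced, because no standard deviation or event rates are given. With n = 2(1.96 + 0.84)² SD²/0.210², a result of 48 needs SD of about 0.367 without dropout. It needs about 0.327 if 38 teeth are to be evaluable and 38/0.8 is rounded up to 48. Neither version contains clustering.

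**1. All of a patient's teeth in one arm.** The design effect is DE = 1 + (m − 1)r and the effective number of teeth is 48/DE. The last two columns are simulated sizes of the two-proportion test at nominal 5%. Power assumes that 48 independent teeth would give 80% and that the standard error is correct.

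| m | r | DE | 48 teeth worth | Power | Size, same arm | Size, tooth-by-tooth |
|---|---|---|---|---|---|---|
| 2 | 0.3 | 1.3 | 36.9 | 0.69 | 7.7% | 5.5% |
| 2 | 0.5 | 1.5 | 32.0 | 0.63 | 9.6% | 5.2% |
| 3 | 0.3 | 1.6 | 30.0 | 0.60 | 10.7% | 5.3% |
| 3 | 0.5 | 2.0 | 24.0 | 0.51 | 13.4% | 5.2% |
| 4 | 0.3 | 1.9 | 25.3 | 0.53 | 12.9% | 4.9% |
| 4 | 0.5 | 2.5 | 19.2 | 0.43 | 17.1% | 5.4% |

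The simulated sizes agree with theory. Splitting a score at its median turns r into (2/π)arcsin(r), which is 0.194 for r = 0.3 and 0.333 for r = 0.5. Then DE is 1 + 0.194 = 1.19 at m = 2 and 1 + 3 × 0.333 = 2.0 at m = 4. The size 2[1 − Φ(1.96/√DE)] is 7.3% and 16.6% respectively.

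**2. Each tooth allocated at random, ignoring the patient.** The last column shows that the between-arm size stays near 5%. The loss is precision. The variance of a between-arm contrast from a model with a patient effect, relative to the unclustered analysis, is approximately (1 − r)(1 + (m − 1)r)/(1 + (m − 2)r):

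- m = 2, r = 0.3: 0.7 × 1.3/1.0 = 0.91, so 9% of the variance is avoidable.
- m = 4, r = 0.5: 0.5 × 2.5/2.0 = 0.625, so about 37%.

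Simulation gave 0.915 and 0.627.

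When stratification on baseline score was added to the simulation (assumed baseline to follow-up correlation 0.6) and ignored in the analysis, the size was 2.5 to 3.7%. It was already 3.1 to 3.2% with one tooth per patient, so that drop comes from the stratification and not from clustering.

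**3. A patient's teeth forced into different arms.** The test becomes conservative, with simulated sizes from 4.5% (m = 2, r = 0.3) down to 1.5% (m = 4, r = 0.5).

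**4. Time points within one treatment.** The same teeth are compared by an unpaired test, so positive correlation over time makes the standard error too large. Simulated with clustering and tooth-by-tooth allocation, the size is about 1 to 2% at an assumed between-time correlation of 0.6 and about 3.5 to 5.5% at 0.3.

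**5. One tooth per patient.** DE = 1 and the clustering problem disappears. Item 4 remains.

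**The case against.** The strongest reply is that section 3.3 lists, orders and stratifies teeth, and section 3.4 treats a single tooth, so allocation is most naturally tooth by tooth. The between-arm tests then hold their level, and all that is lost is efficiency. This stands.

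A reader might infer that the plan inflates false positives, by up to about 17%, or about 22% from the design-effect formula for a t-test on the scores. The documents do not support that as a finding. The inflation needs a patient's teeth to share a product, which the protocol neither states nor excludes, and section 3.6 names no t-test. A reader might also infer that the within-treatment comparisons are too liberal. Clustering alone would push the variance of a single arm's mean that way, but the planned test compares the same teeth over time, and there the pairing it ignores usually dominates.

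It is also fair that the extent is unknown. At least one exposure is an eligibility floor, and most patients might supply one tooth. At 1.5 teeth per patient and r = 0.2 the design effect is only 1 + 0.5 × 0.2 = 1.10. But nothing in the text limits patients to one tooth, and counting recruitment in teeth without a number of patients leaves the matter open.

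**Conclusion.** The concern holds in a limited form. The protocol allows several teeth per patient, makes the tooth the unit and names tests that ignore both the patient and the repeated measurement of each tooth.

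- On the natural reading, the cost between arms is lost precision and not a wrong error rate.
- On the reading where one patient has one product, the cost is a materially inflated error rate and far less information than 48 teeth suggest. Power with a correct standard error would be about 0.43 to 0.69 instead of 0.80, which is more than a slight loss.
- The time-point tests use the wrong standard error on either reading and are mostly conservative, so real change within a treatment could be missed.

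Every size given here rests on assumed teeth per patient, ICC and between-time correlation. What is certain from the text is that the named tests do not fit the data structure the protocol permits, and that the allocation rule deciding the direction of the error is not stated.

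**What to change.** **Section 3.6.** Replace the two-proportion tests with a mixed model of the VAS and CoVAS scores. Include treatment, time and their interaction, with random intercepts for patient and for tooth within patient. GEE clustered on patient with robust standard errors is an alternative. Naming the score as the outcome also removes the need for a cut-off, which the protocol does not give. Obtain the confidence interval for the VAS–CoVAS correlation by resampling patients.

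**Section 3.3.** Carry the patient identifier in the randomisation spreadsheet, and state how several teeth of one patient are allocated (same product, different products, or independently).

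**Section 3.2.** Report the number of patients beside the 192 teeth. Restate power on the effective number of teeth under a stated teeth-per-patient figure and ICC.

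**Cost.** Protocol wording, one spreadsheet column and a different model. No extra enrolment is required, but the quoted power may fall appreciably if a patient's teeth share a product.

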|                                                                                                                                                                                                             | -Use of analgesics or anti-inflammatory drugs                                             |

Following the guidelines of the Federal Council of Dentistry for clinical care during the COVID-19 pandemic, the following protocol will be adopted: patients will be scheduled at staggered times to avoid crowding; 70% alcohol solution will be available in waiting areas for hand hygiene; face masks will be mandatory; the clinical environment will be disinfected between appointments from the least contaminated to the most contaminated areas (reflector handle, chair, stool, assistant cart surface, and dental unit, respectively); PVC barriers will be applied to contact surfaces (mechanical buttons, reflector handles, chair backrests and armrests, stool backrest, handpieces, three-way syringe body, and suction tips); all instruments will be disinfected with enzymatic detergent and sterilized.

Researchers will wear impermeable disposable gowns, disposable caps, protective goggles, surgical masks (for non-aerosol procedures), PPF or N95 masks (for aerosol-generating procedures), face shields, and gloves, all changed after each appointment. Regarding air-jet sensitivity testing in root exposures, relative isolation with cotton rolls will be used, and adjacent teeth will be covered with insulating tape (Isotape, TDV Dental, Pomerode, Santa Catarina, Brazil). The stimulus will consist of an air jet delivered by a three-way syringe positioned 1 cm from the cervical region for a maximum of 2 s. Immediately afterward, patients will indicate sensitivity level on the VAS, which consists of a 10 cm horizontal line where pain is scored from 0 to 10 points: 0 = no pain, 1–3 = mild pain, 4–6 = moderate pain, and 7–10 = severe pain. Patients will mark a vertical line across the horizontal scale to indicate DH intensity. The distance in mm from the zero endpoint will be measured with a millimeter ruler. Teeth with at least grade 3 sensitivity on the VAS will be included.

After selection, each patient will receive and sign an informed consent form (in duplicate), detailing study objectives and procedures.

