The CoVAS will then be used by applying a constant air-jet stimulus, 10 mm from the vestibular surface of the teeth, for 15 s. During this period, the patient will record discomfort intensity on a 0–100 scale using a manually controlled potentiometer. Sensitivity analyses (VAS and CoVAS) will be recorded at baseline. All participants will receive a soft-bristle toothbrush and a non-desensitizing toothpaste for use throughout the study.

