### 3.4 Clinical Procedures

After baseline assessments, a lip and cheek retractor will be placed. The tooth receiving the desensitizing agent will be isolated with cotton rolls and dried with an air jet, with moisture controlled by suction. The assigned product will be applied in two layers with a microbrush and left on the surface for 10 minutes. Light-cured products will be photoactivated for 10 s (LED Radium-cal, SDI Brasil Indústria e Comércio LTDA, São Paulo, Brazil). Afterward, cotton rolls and the retractor will be removed.

At the end of the study, if experimental treatments are ineffective in reducing dentin hypersensitivity, patients will be treated with the product that shows the best results to avoid further complications.

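### No VAS reading on the treatment day is described; if the selection reading is the baseline, within-product change includes regression to the mean, and the exposure-height strata conflict with batch-wise allocation

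*Protocol*

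**What the plan says.** **Selection.** Protocol section 3.2 describes an air-jet test followed by a VAS mark, and then: "Teeth with at least grade 3 sensitivity on the VAS will be included". Consent comes next, then the CoVAS, and then: "Sensitivity analyses (VAS and CoVAS) will be recorded at baseline". Section 3.1 places baseline before treatment and sets no maximum interval.

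**Allocation.** Section 3.3 states: "Root exposure height and sensitivity scores by VAS will be stratification variables in the randomization process". It adds: "Eligible teeth will be entered into an Excel spreadsheet according to root exposure height and mean sensitivity score". For the split, "teeth will be ordered by sensitivity scores and divided into two clusters: one with lower scores and the other with higher scores". Each half is then divided by smaller or larger exposure, giving four strata. On timing: "Stratification will be performed approximately every 48 selected teeth for methodological feasibility".

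**Exposure height.** The same section says the measured heights are not classified at that stage: "scores will be established only after the complete sample has been obtained".

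**Treatment and follow-up.** Section 3.4 opens: "After baseline assessments, a lip and cheek retractor will be placed". It gives no day or visit and no new VAS or CoVAS reading. Section 3.5 covers only the follow-up visits from day 7.

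**Analysis.** Null hypothesis (b) in section 2 concerns differences across time points within one product. Section 3.6 tests both the between-product and the within-product comparisons with two-proportion tests at 5%. All four arms receive a product; none is untreated.

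**The concern.** A formal before-and-after hypothesis needs a fixed 'before' value. The protocol describes a single VAS procedure ahead of treatment, and that procedure decides whether the tooth enters. When teeth are admitted because one noisy reading reached a threshold, a second reading is lower on average even if nothing was done. If the admitting reading is also the baseline, all four products share this fall. With no untreated arm to show it, each could appear to reduce hypersensitivity.

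The age of the reading is a second and separate matter. A tooth cannot be ranked until its batch exists, so a tooth measured early in a batch waits before it can be assigned a product.

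The third matter is internal to section 3.3. Strata formed at each batch need the smaller/larger split at that time, but the text puts classification of height off until sampling is complete.

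**Working it through.** **How many pre-treatment readings are described.** Section 3.2 has one VAS procedure, used for inclusion. Its later sentence on recording VAS and CoVAS at baseline describes no second VAS procedure. Section 3.3 carries the baseline heading but lists only DMFT, plaque index, bleeding index and exposure height as new measurements. Section 3.4 goes to isolation and application. The VAS used for ranking must precede allocation, and nothing later is described until day 7.

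**The plan's own figures.** 4 arms × 48 teeth = 192, as stated, and 192 / 48 = 4 allocation batches. The protocol gives no VAS mean, SD, reliability or baseline-to-treatment interval, so the sizes below rest on stated assumptions.

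**Wait caused by batching.** In the implementation schedule (section 4), Step B runs over months 1 to 5 and includes the 30-day visit. That leaves about 4 months for selection and application. Assuming even accrual:

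- 192 / 4 = 48 teeth a month, so a batch takes about one month to fill.
- The first tooth in a batch waits about 4.3 weeks, and the average tooth about half that, roughly 2 weeks.
- With 3 to 5 months of accrual the longest wait is 3.3 to 5.4 weeks.

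**Regression to the mean.** For selection at VAS ≥ 3 on the same reading that serves as baseline:

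expected fall = (1 − r) × SD × φ(z) / (1 − Φ(z)), with z = (3 − mean) / SD.

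Here r is the correlation between two readings on the same tooth without treatment. Assumed: SD 2, population mean 4, 5 or 6, r from 0.5 to 0.9.

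- Mean 4: z = −0.5; 2 × 0.3521 / 0.6915 = 1.018
- Mean 5: z = −1.0; 2 × 0.2420 / 0.8413 = 0.575
- Mean 6: z = −1.5; 2 × 0.1295 / 0.9332 = 0.278

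Multiplying by (1 − r):

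| Mean | r = 0.5 | r = 0.7 | r = 0.8 | r = 0.9 |
|---|---|---|---|---|
| 4 | 0.51 | 0.31 | 0.20 | 0.10 |
| 5 | 0.29 | 0.17 | 0.12 | 0.06 |
| 6 | 0.14 | 0.08 | 0.06 | 0.03 |

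Letting SD run from 1.5 to 2.5 as well widens the range to 0.01 to 0.70. A simulation on a 0–10 scale with no treatment effect agrees: 0.306 at mean 4 and 0.173 at mean 5, both with SD 2 and r 0.7. The wait does not enter the formula. It can act only indirectly, by lowering r.

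**What this does to a within-product test (illustration only).** Take a paired test of means with 48 teeth treated as independent, two-sided at 5%, SD 2 and r 0.7.

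- Mean 4: the SD of the differences is 1.48, so SE = 1.48/√48 = 0.214 and 0.306/0.214 = 1.43. The chance of a significant fall is 1 − Φ(1.96 − 1.43) ≈ 0.30.
- Mean 5: the same steps give 0.12.
- With no regression to the mean, a significant fall would occur 2.5% of the time.

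Section 3.6 plans a two-proportion test and does not define the proportion. If it were the share of teeth with VAS below 3 (an assumption), baseline would be 0% by selection. At retest with no effect the share would be 16% (mean 4, r 0.7) or 9% (mean 5, r 0.7), and the test would reject in 96% or 63% of trials. At mean 6 and r 0.8 it would reject in 8%.

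**Height classification.** One sentence postpones it to the end of sampling. The stratification steps in the same section need it four times, once per batch. As written, both cannot be followed.

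**The case against.** **The protocol does not say that the selection reading is the baseline.** This is the strongest objection, and it stands. Section 3.2 puts consent between the selection VAS and the sentence on baseline recording, and section 3.3 speaks of a mean sensitivity score, which hints at more than one reading. A reader might take the shared reading as established, but it is only the most natural interpretation, and the conclusion is therefore conditional. Averaging would raise r and shrink the fall. It would not remove the fall if the same readings decided entry.

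**Batching does not cause the inflation.** A reader might infer that the weeks of waiting inflate within-product change. They do not. The inflation comes from selecting on the baseline value and would arise with same-day allocation. The wait makes the value out of date, with drift possible in either direction.

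**Sections 3.3 and 3.4 need not conflict.** A reader might take section 3.4 to mean treatment at the baseline visit, but it names no visit, and a later treatment visit fits both sections.

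**The size is uncertain.** Mean, SD and correlation are all assumed, and at the favourable end the fall is negligible. Measuring it against the planned difference of 0.210 is tempting. If that figure is a between-arm difference, however, a fall common to all arms cancels from it. The paired test is not the planned test.

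**The height sentence may be loose wording.** It might refer to descriptive scoring, or use 'complete sample' for a batch. Either is possible, and neither is written.

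**Adjustment for strata is often left to the SAP.** That is fair as a general rule. Here, though, section 3.6 already names an unadjusted two-proportion test, so it is raised only as a secondary matter.

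**Conclusion.** The point holds in conditional form. The protocol describes one pre-treatment VAS reading, uses it for inclusion and batch-wise stratification, and describes no re-measurement on the treatment day. If that reading is the baseline, within-product change includes a spurious fall of about 0.03 to 0.51 VAS points under SD 2, mean 4 to 6 and r 0.5 to 0.9. The reading would also be up to about 4 weeks old, about 2 on average, at even accrual over about 4 months.

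The harm is confined to null hypothesis (b) and to statements that a product reduces hypersensitivity. A reader might extend it to null hypothesis (a), but the documents do not support that: all arms share the threshold and the batching, and are randomised, so the between-arm comparison is not biased.

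The height-classification sentence conflicts as written with stratification at each batch. The point should be settled before enrolment, because a pre-treatment reading that was not taken cannot be recovered.

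**What to change.** 1. **Define the baseline reading.** In sections 3.1 to 3.4, use the selection VAS for eligibility and strata only. Define baseline as VAS and CoVAS taken at the treatment visit, immediately before application, and keep teeth in the analysis whatever that second reading shows. This brings the regression-to-the-mean component to about zero and removes the staleness. The cost is protocol wording and one extra short air jet; the CoVAS is moved, not added.

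2. **Reconcile the height sentence.** State in section 3.3 that both the sensitivity split and the exposure split are made within each batch, and remove or reword the sentence that delays classification. This costs wording only.

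3. **Secondary: use the randomisation factors in the analysis.** In section 3.6, replace the unadjusted between-arm test with a comparison of VAS adjusted for baseline VAS and root exposure height. Both are already collected. The benefit is precision. It changes the analysis method, since a two-proportion test cannot carry these covariates.

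A fresh baseline does not remove placebo response or natural course from within-product change. The protocol should therefore say that conclusions about efficacy rest on the between-arm contrasts.
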